## Abstract

**Background:**

Radiation therapy (RT) results in pain relief for about 6 of 10 patients with cancer induced bone pain (CIBP) caused by bone metastases. The high number of non-responders, the long median time from RT to pain response and the risk of adverse effects, makes it important to determine predictors of treatment response. Clinical features such as cancer type, performance status and pain intensity, and biomarkers for osteoclast activity are proposed as predictors of response to RT. However, results are inconsistent and there is a need for better predictors of RT response. A similar argument can be stated for the development of cachexia; there are currently no predictors that can identify patients who will develop cachexia later in the cancer disease trajectory. Experimental and preclinical studies show that pain, depression and cachexia are related to inflammation. However, it is not known if inflammatory biomarkers can predict CIBP, depression or development of cachexia.

**Methods:**

This multicenter, multinational longitudinal observational study will include 600 adult patients receiving RT for CIBP. Demographic data, clinical variables, osteoclast and inflammatory biomarkers will be assessed before start of RT, and 3, 8, 16, 24 and 52 weeks after last course of RT. The primary aim of the study is to identify potential predictors for pain relief from RT. Secondary aims are to explore potential predictors for development of cachexia, the longitudinal relationship between pain intensity and depression, and if inflammatory biomarkers are associated with changes in pain intensity, cachexia and depression during one-year follow up.

**Discussion:**

The immediate clinical implication of the PRAIS study is to identify potential predictive factors for a RT response on CIBP, and thereby reduce non-efficacious RT. Patient benefits are fewer hospital visits, reduced risk of adverse effects and more individualized pain treatment. The long-term clinical implication of the PRAIS study is to improve the knowledge about inflammation in relation to CIBP, cachexia and depression and potentially identify associations and mechanisms that can be targeted for treatment.

**Trial registration:**

ClinicalTrials.gov NCT02107664, date of registration April 8, 2014 (retrospectively registered).

## Background

### Cancer induced bone pain (CIBP)

Pain is one of the most frequent symptoms among cancer patients [1]. About half of cancer patients with pain are not adequately treated [2, 3]. Pain and other symptoms represent a heavy burden on the patients, their families and also on the health care system. Bone metastases account for up to 70% of cancer related pain [4, 5].

Cancer induced bone pain (CIBP) often present as a combination of somatic and neuropathic pain [6]. When tumor masses expand inside bone it can cause pain by stretching of the periosteum, fractures or invasion of sensory nerves [7]. Tumor cells also release pro-inflammatory cytokines, nerve growth factors and increase oxidative stress in the bone microenvironment. The alternation of biological substances in the bone microenvironment influence pain perception by activation of glia cells, sensitization of somatic nerve endings and disruption of the normal bone homeostasis with a balanced osteoclast and osteoblast activity [8]. Secretion of biological substances from tumor cells may also influence the central nervous system and trough immune modulation change perception of pain and the efficacy of opioids [9].

### Prediction of RT response in patients with CIBP

Palliative radiation therapy (RT) is a major treatment modality for cancer induced bone pain (CIBP), often together with opioids and co-analgesics [10]. Unfortunately, not all patients experience pain relief after RT. Complete pain response is reported in about one quarter of the patients, and partial pain response in 40–60% [11, 12]. Median time to pain response is 1 to 4 weeks [13]. RT are in most cases not associated with severe adverse effects, but nausea and vomiting is reported in up to 77% of patients [14], and pain-flares during and after RT is reported by up to one third of the patients [15, 16]. Diarrhoea, skin reactions, lethargy and tiredness are also potential adverse effects after RT [11].

Based on a relative high number of patients not responding to RT, time to treatment effect and the risk of potential side effects it is important to identify potential predictors for RT response. Former RT trials have used different pain assessments and different definitions for RT response. An international consensus on endpoints in RT trials were first published by Chow et al. in 2002 and updated in 2012 and have resulted in more comparable RT trials [17, 18]. Two recent papers on rather large patient materials found that patients with breast or prostate cancer and higher performance status were more likely to respond to RT. High baseline pain scores, the use of morphine, absence of visceral metastases and younger age were also associated with RT response in one out of the two papers [19, 20].

Imaging techniques may also be helpful to predict RT response. Two studies have demonstrated that low uptake on FDG PET-CT before RT predicted better RT response [21, 22]. MRI have also been proposed to predict RT response, but the published results are so far inconsistent [23, 24]. In addition both PET and MRI is time and economically difficult to establish as routine care. Biomarkers such as urinary osteoclast markers have been proposed to predict RT response in patients with bone metastases [25, 26], but this association is not present in all trials [27]. Elevated C-reactive protein (CRP) levels are related to more advanced disease in cancer patients that undergo palliative RT, but as far as we know no studies demonstrate a relationship between the level of CRP or other inflammatory markers and RT response in patients with CIBP [28]. Previous published literature on clinical predictors for response to RT has also no information about radiographic appearance of metastases like sclerotic/osteolytic metastases, soft tissue expansion outside bone, other cancer related symptoms or biomarkers as potential predictors.

Thus, there is still not enough information to predict which patients who are likely to respond poorly, and consequently should not receive RT. To identify patients who have increased likelihood of successful analgesia from palliative RT would improve cancer pain management.

### Cancer related symptoms and the role of inflammation

In recent years there has been an increased interest among researchers to understand the correlation between the immune system and development of cancer and cancer-related symptoms. Inflammation is present in the majority of patients with advanced cancer [29], and it is therefore difficult in cross sectional studies to establish if inflammation is simply associated with severity of the cancer disease, or whether inflammation itself elicits symptoms and can be a target to reduce symptoms like pain, depression or cachexia [30].

#### Cancer induced bone pain and the role of inflammation

Based on results from pre-clinical studies several inflammatory mediators are proposed to play an important role in CIBP. The pro-inflammatory interleukin (IL)-1β, IL-6 and tumor necrosis factor (TNF)-α are associated with nociception in animal models of bone cancer [31, 32]. Other inflammatory mediators, including chemokines such monocyte chemoattractant protein (MCP)-1, macrophage inflammatory protein (MIP-1)α, and the anti-inflammatory cytokine transforming growth factor (TGF)β, are upregulated in animal models of bone metastases, and receptors for cytokines are also present on the osteoclast surface. The release of inflammatory cytokines from tumor cells may therefore contribute to osteoclast activation with CIBP as a consequense [8, 33]. Some studies have demonstrated a potential role of inflammation (CRP, IL-6) for general cancer pain [34–36]. but as far as we know there are no published clinical trials on inflammation in relation to CIBP.

#### Development of cachexia and the role of inflammation

Up to 80% of patients with advanced metastatic cancer develop cachexia, and approximately 20 % of cancer deaths are attributed to cancer cachexia [37]. Cancer cachexia has a significant impact on patient morbidity as these patients often have reduced physical function, increased fatigue and psychosocial distress. According to a recent international consensus cachexia has been defined as a multifactorial syndrome characterized by an ongoing loss of skeletal muscle mass (with or without loss of fat mass) that cannot be fully reversed by conventional nutritional support and leads to progressive functional impairment [38]. In the consensus document, cachexia is described as a trajectory from early cachexia to late cachexia, and treatment should be assigned to patients according to the different stages. A longitudinal observational study is required to establish which factors predict both the cachexia syndrome and late cachexia.

The complete pathophysiology behind cachexia is still unclear. Most studies on molecular mechanisms have been performed on different animal models; studies in humans are scarce. Anemia, low serum albumin and increased inflammatory biomarkers such as CRP, TNF-α, soluble TNF-receptor 1 (sTNF-R1), IL-1, IL-6 and interferon (IFN)-gamma are observed in patients with cachexia [39]. Inflammatory markers such as TGFβ involved in development of bone metastases is probably also important in development of cachexia [40]. However, systemic inflammation is seen in a majority of patients with cancer, and not all of them develop cachexia therefore as for pain longitudinal studies are needed.

#### Depression in patients with advanced cancer and the role of inflammation

Depression disorder contribute to reduced quality of life in patients with advanced cancer [41]. Depression disorder is common among cancer patients with a prevalence that varies from 5 to 30% between studies [42]. A particular challenge for assessment of depression in patients with advanced cancer is the somatic depression symptoms (fatigue, psychomotor retardation, appetite disturbance and sleep disturbance) which constitute 4 out of 9 diagnostic criteria for depression disorder. In patients with advanced cancer the somatic depression symptoms can result from depression, the cancer, treatment effects, or a combination of these factors [43].

In a cross-sectional study that also controlled for disease load, we demonstrated that by only using the 5 psychological depression symptoms for defining depression disorder, we could circumvent the challenge of the overlap between the somatic depression symptoms and symptoms of the cancer [44] [45]. However, our study was cross-sectional thus limiting the possibility to assess causality [44]. Studying the development of depression disorder and each of the depression symptoms over time with control for disease and treatment(s) can provide evidence-based guidance on how to best assess depression in patients with advanced cancer.

Patients with advanced cancer and depression disorder have more somatic symptoms including pain compared to non-depressed patients, but no appropriately designed studies to examine a possible causal relationship have to our knowledge been published. Clinically, a common observation is that long-lasting pain is associated with increased levels of depression symptoms. Still the direction of causality is not established and might be bidirectional. The relation between pain and depression has to be studied in a longitudinal design in order to better understand how they are related.

Behavior corresponding to the depression symptoms, such as lowered mood, anhedonia, fatigue, sleep and appetite alterations, are also observed as a response to infections in mammals and then termed sickness behavior. Sickness behavior has been recognized as a symptom cluster that is associated with pro-inflammatory cytokine activation [46]. In non-cancer patients depression disorder has been linked to inflammation and oxidative stress [47]. Meta-analyses have demonstrated that IL-6, TNF, and CRP are elevated in non-cancer patients with depression disorder [48]. A limited number of studies have demonstrated increased levels of cytokines (IL-6, IL-8,TNFα) in cancer patients with depression [49, 50]. These findings need verification in studies using a validated measure of depression and controlling for disease and other factors known to affect the inflammatory response.

### The palliative radiotherapy and inflammation study (PRAIS)

As cancer treatment develops, a wider range of treatment options are available to each patient, and the need for tools to determine treatment response arises to select the right individual treatment. The primary aim of the PRAIS study is to combine clinical and biomarker predictors to predict the response to RT for patients with CIBP.

The availability and indications for new cancer therapeutics that modulates the immune system in order to delay development and even cure cancer have increased the last years, and a better understanding of the role of systemic inflammation in relation to cancer and cancer associated symptoms are of interest when the field of immunotherapy develops. To better understand complexity of systemic inflammation one need to extrapolate knowledge from pre-clinical studies to clinical studies with a robust study design. Secondary aims of the PRAIS study are, therefore, in a longitudinal study to explore the relationship between cancer related symptoms and inflammatory biomarkers during a one-year follow up.

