### Study objectives

The primary aim of the PRAIS study is to investigate clinical and biomarker predictors of pain response after palliative RT for CIBP. In the secondary analyses of this longitudinal study we will explore association between inflammation and pain intensity, cachexia, and depression in patients with CIBP that undergo palliative RT, factors associated with development of cachexia in one-year follow up and correlation between pain intensity and depression (Fig. 1).

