### Outcome and statistical analyses

For all planned analyses baseline data will be presented with descriptive statistics; continuous variables as mean with standard deviation and categorical variables as frequency with percentages. A detailed overview of research questions and statistical analyses are described in the following section. All analyses will be performed using SPSS v 23 (IBM Corp. Armonk, NY) and STATA v 16 (Stata Corporation LP; College Station, TX, USA).

**Research question 1:** Which are the clinical predictors and biomarkers predictors of pain response to palliative RT for CIBP?

*Objective*: To obtain demographic, clinical data and biomarkers before start of RT and compare with RT response for pain in order to develop a classification system relevant for predicting RT response.

*Outcome*: Primary endpoint is response to RT defined as at pain reduction of worst pain score of two or more at the treated site on the 11-point NRS together with no increase in analgesic intake, or a reduction in opioid intake of at least 25% from baseline without an increase in worst pain score at the treated site [18]. Patients with two or more radiation locations are defined as responders if they respond in one of the included sites. Patients who die before the first assessment (3 weeks after RT), will be defined as non-responders because these patients have not benefited from RT. Patients with missing data on outcome measurements including pain intensity at the treated site or the use of analgesic medications will not be included in the analyses.

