*Statistical method*: Clinical variables (see previous chapter) and CRP will be included in a multivariate logistic regression model to predict potential factors for response to RT. The model will be adjusted by study centre. Regression diagnostics will be performed for all analyses adding interactions terms if necessary. Significant variables from the multivariable model will be presented as a response-score to determine the likelihood of response to RT. Second, we will perform analyses on inflammatory biomarkers and bone biomarkers correlated with response to RT. Only inflammatory biomarkers and bone biomarkers with levels of serum concentrations above the detection threshold and which have a variability between measurements will be analysed with a multivariate logistic regression model with response to RT as the dependant variable. Finally, an integrated regression model with response to RT including both the significant clinical variables and significant biological biomarkers will be conducted if appropriate based on results from the previous analyses.

**Research question 2:** Which inflammatory biomarkers are associated with change in pain intensity in patients with CIBP?

*Objective*: To investigate the correlation between pain intensity and inflammation. Patients included in the PRAIS study all have CIBP and will receive a standardized intervention expected to give pain relief in about 60% of the patients. This study can explore if there is a longitudinal relationship between changes in pain intensity and the detected level of inflammatory biomarkers.

*Outcome*: Serum concentrations of inflammatory biomarkers as described above associated with changes in pain intensity as measured by average pain intensity and worst pain intensity last 24 h (NRS 0–11) for a maximum of 1 year follow-up.

*Statistical method*: Longitudinal data analysis with repeated measurements using a liner mixed effect model or generalized estimating equation (GEE).

**Research question 3:** Which inflammatory substances are associated with cancer cachexia?

*Objective*: To gain insight into the role of inflammation in cancer cachexia.

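### The only model joining clinical predictors with the cytokine and bone markers is run at discretion after earlier results, and the only response-score comes from the clinical-plus-CRP model

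*Protocol article*

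**What the plan says.** The protocol article words the primary aim in three ways.

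- Background, section on the PRAIS study: "The primary aim of the PRAIS study is to combine clinical and biomarker predictors to predict the response to RT for patients with CIBP".
- Study objectives: "The primary aim of the PRAIS study is to investigate clinical and biomarker predictors of pain response after palliative RT for CIBP".
- Abstract, Methods: "The primary aim of the study is to identify potential predictors for pain relief from RT".

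Under Outcome and statistical analyses, the objective of research question 1 is to collect demographic data, clinical data and biomarkers before radiotherapy "in order to develop a classification system relevant for predicting RT response".

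The statistical method for that question then has three steps.

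1. "Clinical variables (see previous chapter) and CRP will be included in a multivariate logistic regression model to predict potential factors for response to RT". After remarks on centre adjustment and regression diagnostics comes the score: "Significant variables from the multivariable model will be presented as a response-score to determine the likelihood of response to RT".
2. "Second, we will perform analyses on inflammatory biomarkers and bone biomarkers correlated with response to RT". Markers above the detection threshold and with variability go into a separate logistic model.
3. An integrated model takes the significant clinical variables and the significant markers. It "will be conducted if appropriate based on results from the previous analyses".

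Power consideration and Expected limitations both say that there will be no validation sample.

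**The concern.** The Background wording and the objective of research question 1 call for one prediction tool that draws on clinical and biomarker data together. The only tool the method describes is a score attached to step 1, before any cytokine or bone marker has been analysed. The only model that sets those markers beside the clinical variables is step 3. Whether it is run depends on the data, and the text gives no rule for deciding.

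Two outcomes are then possible. Step 3 may be left out, and a clinical-plus-CRP score published with no estimate of what the other markers add. Non-significance of single markers does not show that the set adds nothing. Or step 3 may be run on variables chosen for their significance in the same data, and the apparent gain would then be too favourable. With no validation sample, the study has no separate data in which to detect this.

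**Working it through.** **What each step delivers**

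| Step | Predictors | Always run? | Score stated? |
|---|---|---|---|
| 1 | Clinical variables, CRP | Yes | Yes |
| 2 | Inflammatory and bone markers | Yes | No |
| 3 | Significant variables from 1 and 2 | Only if judged appropriate | No |

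Steps 1 and 2 meet an aim of identifying or investigating predictors. Only step 3 meets an aim of combining clinical predictors with markers other than CRP.

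**Markers outside the score.** Table 2 lists 29 inflammatory markers, including high-sensitivity CRP, and 4 bone markers: 29 + 4 = 33. Without high-sensitivity CRP, 32 remain. None of these is in the step 1 model.

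**The plan's own sizing.** Power consideration uses 10 patients per variable with 29 clinical variables: 10 × 29 = 290, which reproduces the stated figure. Allowing for 20% loss gives 290 / 0.80 = 363. The rest of the way to 600 is an unquantified allowance for interactions. The 290 counts neither CRP nor any other marker.

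- Patients left after 20% loss: 600 × 0.80 = 480. By the plan's rule that supports 480 / 10 = 48 predictors.
- Clinical variables plus CRP: 29 + 1 = 30. Room for markers: 48 − 30 = 18, before centre terms and interactions.
- All 32 markers added: 30 + 32 = 62 predictors. The rule would need 620 analysed, or 620 / 0.80 = 775 recruited.

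**How step 3 depends on chance.** The article gives no significance level and does not say how many markers will pass the filter. I assume 0.05 and independent tests.

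If no marker has any effect, the chance that none is significant is 0.95^m:

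- m = 32: 0.19, so at least one is significant in 81% of studies
- m = 20: 0.36, so 64%
- m = 15: 0.46, so 54%

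Now suppose that four markers truly predict response, with odds ratio 1.2 per SD and variance inflation of 2 to 3 (assumed). Take 480 analysed and the 60% response that the plan expects.

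- Information: 480 × 0.6 × 0.4 = 115.2
- SE of the log odds ratio: √(2/115.2) = 0.132 to √(3/115.2) = 0.161
- ln 1.2 = 0.182, so power per marker is about 28% down to 20%
- All four missed: (1 − power)^4 = 0.27 to 0.40
- No marker at all significant, with 28 null markers as well (0.95^28 = 0.238): 0.27 × 0.238 to 0.40 × 0.238, or about 6 to 10%. With 20 markers retained it is 12 to 18%, and with 15 it is 15 to 23%.
- All four missed but at least one null marker significant (32 retained): 0.27 − 0.06 to 0.40 − 0.10, or roughly 20 to 30%. Step 3 would then contain only chance findings among its markers.

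**What might go unestimated.** Take AUC = Φ(SD of the linear predictor / √2), with an assumed SD of 0.7 for the clinical part: AUC 0.69. Four such markers add variance 4 × 0.182² = 0.133 and bring it to 0.71. Six markers at odds ratio 1.3 bring it to 0.75. These figures treat the coefficients as known, so an estimated model would gain less in new patients.

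**The case against.** The strongest reply is that the formal Study objectives section asks only for an investigation of predictors, and that the Abstract and the question itself say much the same. Steps 1 and 2 answer that and are always run. This stands. A reader might infer that the primary aim may never be answered, but the documents support that only for the Background wording and the classification objective, and only for markers other than CRP.

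CRP also counts. Table 2 lists it under clinical chemistry and, in its high-sensitivity form, among the inflammatory markers. Step 1 therefore already joins clinical variables with one inflammatory marker, and it would be wrong to call its score purely clinical.

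It can further be said that tying the score to step 1 rests on sentence order, and that a fuller plan may hold the trigger and name the final model. That has weight for details that are merely absent. It does not remove the condition itself: the article states that step 3 depends on earlier results.

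A staged analysis is also defensible, since the Discussion calls the inflammation work exploratory. The same Discussion, however, presents inflammatory and bone markers as data that could help select patients in routine practice, and that needs an estimate of what they add.

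Two further inferences should be resisted. The 27 to 40% above is not the chance that step 3 is skipped. It is the chance that all four assumed true markers are missed, and it treats their estimates as independent although variance inflation of 2 to 3 implies correlation. Nor does the remedy follow that every marker should enter unpenalised: up to 62 predictors would break the plan's own rule of 10 per variable.

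**Conclusion.** The point holds in a limited form. The primary aim is worded inconsistently. The one model that serves its strongest wording depends on earlier results with no criterion, and no score is stated for it. The added value of the 32 markers other than high-sensitivity CRP may never be estimated, or may be estimated only after selection on significance and without validation.

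This rests on the text and not on the illustrative probabilities. Those depend on an assumed significance level, independence, effect sizes and number of markers retained, and they range widely. What they show is that significance at step 2 is a poor trigger: it can fire on noise and can miss real signal. The matter should be corrected, but it does not invalidate steps 1 and 2.

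**What to change.** 1. Use one wording of the primary aim in the Abstract, the Background and Study objectives.
2. Delete the condition that makes the integrated model depend on earlier results, and fit it whatever steps 1 and 2 show.
3. Enter the markers that pass the detection and variability filter. Limit their number or penalise the model so that the predictor count respects the sample size (about 18 marker terms by the plan's own rule, fewer once centre terms and interactions are counted). Do not select markers on their significance for the outcome.
4. Report the change in AUC and in calibration over the clinical-plus-CRP model, corrected for optimism (for example by bootstrap), with a confidence interval.
5. State in advance which model yields the final response-score, and show the clinical-plus-CRP score beside it as comparator.

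The cost is a change of wording and somewhat more analysis on data already collected. The downside for the authors is that a small or null added value of the markers must then be reported.
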